### Fidelity

Therapists and their supervisors will be asked to adhere to a detailed treatment manual containing session plans, handouts, worksheets, and therapist guidance. The first author will be available for *ad hoc* secondary consultation and advice on applying the treatment and to resolve any technical problems with smartphone surveys. Therapist competence will not be assessed in the study protocol, but therapists are required to attend weekly individual supervision in their clinic placement. Adherence will not be assessed directly, but therapists will be instructed to complete a tracking survey after each session to record any significant deviations from the manual. A researcher will monitor and respond to data quality concerns but will not have access to the clinical record. Participant compliance and exposure dose will be indicated by the number of exposures recorded by the participant using smartphone EMA. Participants will be asked each session whether they didn’t record any exposures using their smartphone, and if so, how many.

### Analysis

The relationship between exposure processes and outcome variables over time will be explored using univariate multilevel modeling (MLM). This modeling framework has a range of strengths for our purposes. It can account for data dependencies typical in longitudinal designs, can handle assessment schedules that are unevenly spaced, and can handle unbalanced data (88). Prediction error is the exposure process of interest. We operationalize prediction error as the discrepancy between threat prediction (P) and threat outcome (O) scores for an exposure.

Prediction error effects can only be explored if enough cases of prediction error exist in the data. We will explore how many cases of prediction error and what type are present in the data before modeling. For descriptive purposes, we will categorize a prediction error as an exposure where the standardized P and O scores differ by more than 0.5 standard deviation in either direction (89). We will proceed with modeling prediction error effects if more than 10% of exposures meet the above prediction error criteria (49).

The primary aim of the study is to explore how prediction error during exposures relates to session-by-session symptom change. Exposures may occur from sessions 5 to 12. The outcomes are measured once at each session, but the number of exposures completed may vary significantly over treatment. We will aggregate EMA data obtained between sessions (e.g., between sessions 5 and 6, or 6 and 7, etc.) to form seven time points. Symptoms at time *t* will be regressed onto the mean P and mean O in the preceding inter-session interval (i.e., between *t* – 1 and *t*). We will control for the effect of symptoms at the preceding session (*t* – 1) and other theoretically relevant exposure mechanisms, specifically mean fear activation (operationalized as mean peak anxiety minus mean pre anxiety) and mean within-exposure habituation (operationalized as mean peak anxiety minus mean end anxiety) in the preceding inter-session interval. Operationalizing fear activation and habituation in these ways is consistent with most prior research, but we acknowledge the limitations of these indices noted by Bonito et al. (38) and will discuss the results in light of these.

In line with learning theory, we hypothesize that people whose exposures since the last session (*t* – 1) went better than expected will have lower social anxiety symptoms and social threat appraisals at the next session (*t*). Specifically, when holding mean O and other controls constant, higher mean P in the preceding inter-session interval (i.e., between *t* – 1 and *t*) will be associated with lower social anxiety symptoms and social threat appraisals at the next assessment (*t*), on average. Conversely, when holding mean O and other controls constant, lower mean P will be associated with higher social anxiety symptoms and higher social threat appraisals at the next assessment, on average.

Hypotheses will be supported if both the following conditions are met; (1) the fixed effect coefficient for mean O is significantly different from zero and positive in sign and (2) the fixed effect coefficient for mean P is significantly different from zero and negative in sign (52). To determine whether the joint effect of these component variables on the outcome variable is more complex than a linear discrepancy effect, we will run a model including second-order terms (mean P^2^, mean P × mean O, mean O^2^) as predictors (47, 50, 53). Hypotheses will be supported if the simpler model fits the data better than the more complex model. Models will be run in R using the nlme or lmer package. We will use the maximum likelihood estimation method and compare model fit using likelihood-ratio tests.

We will separate within- and between-person information for all time-varying predictors using person-mean centering (90). In this method, the person-mean centered predictors are added to level one and their respective person-means are added to level two. The fixed effect coefficients for the person-mean centered predictors are estimates of purely within-person effects, without being confounded with between-person effects.

We will also consider whether time trends are present in the data by regressing social anxiety and exposure process variables on time in separate analyses. The presence of time trends in time-varying outcomes or predictors can potentially confound any observed relationships between these variables (56). In this study, treatment is designed to cause changes to the outcomes and predictors over time and these changes are of direct theoretical interest. In these circumstances, time de-trending is not recommended because it may artificially suppress the predictor coefficients of interest (90). To be conservative, if there are time trends in any of the predictors or outcomes, we will run a sensitivity test on the final models to determine whether the effects of interest remain after time detrending (by adding time as a covariate) (55, 90).

In principle, the data structure has a three-level nested structure where assessments are nested in participants who are nested in therapists. There may be some degree of correlation between participant assessments within-therapist (91). Therapist-related statistical dependency and therapist effects can be addressed using three-level models (assessments at level one, participants at level two, and therapists at level three). If each therapist in the study has at least two participants, then three-level models will be used (assessments at level one, participants at level two, and therapists at level three). Otherwise, two-level models will be used (assessments at level one and participants at level two) since it would not be possible to distinguish between therapist and participant variance (91). Some therapists may be more effective than others and it is possible (but not plausible) that therapists could moderate the effect of prediction error on the outcome. However, exploring therapist effects is beyond the scope of this study.

The secondary aim of the study is whether the average prediction error experienced during treatment predicts treatment outcome. We hypothesize that participants who experienced greater symptom improvements from baseline to 3-month follow-up will have experienced greater overall threat prediction error in their exposures during treatment. For each participant, we will calculate their mean P and O experienced across all exposures in treatment (termed txP and txO, respectively). The outcome will be symptoms at 16 time points from baseline to 3-month follow-up. We will examine the interaction of assessment point with txP and the interaction of assessment point with txO on the outcome. The hypothesis would be supported if both interactions were significant, and txO is positive in sign and txP is negative in sign. The secondary hypotheses will be exploratory because cross-level interactions likely require larger sample sizes to be adequately powered to detect a medium effect size (92).

The tertiary aim of the study is to explore whether prediction error relates to surprise and learning outcomes. We hypothesize that the larger prediction error (regardless of type) will predict larger feelings of surprise after an exposure and greater likelihood for participants to report a learning outcome. We will use the EMA data without aggregation to perform multi-level RSA with surprise as the outcome and P and O and their higher order terms as predictors. Response surface parameters will be examined to determine whether the hypothesis is supported (49, 50, 53).

We will test whether session modality (in-person vs. video teleconference) affects outcomes by adding it as a level one predictor to all final models. We retain it as a control variable if it improves model fit. We will check the internal consistency of the threat prediction and outcome measures (other exposure measures are single item) using multilevel modeling [see (93)]. We will check the validity of exposure process measures by looking for expected patterns of associations among these variables (94).

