Fear extinction is thought to occur following negative threat prediction errors, defined as when the rate or severity of aversive outcomes is *less than expected* during an encounter (21, 24, 25, 27). Conversely, fear learning is thought to occur following positive threat prediction errors, defined as when the rate or severity of aversive outcomes is *greater than expected* during an encounter (24, 25). Extinction learning is an inhibitory process where new memories are formed to represent the safety of the stimulus rather than old threat associations being “unlearned” (35). New safety associations that are acquired through extinction training compete with prior threat learning for retrieval when a person encounters relevant cues (35). Additionally, new safety associations are linked to their learning context and may not generalize or be retrieved if the stimulus is encountered in a different context (35). Extinction learning being inhibitory and context dependent can explain how, after a course of successful extinction training, fear can return in new contexts or spontaneously after a period of time, and also can return rapidly after subsequent aversive experiences (35).

Craske et al. (12, 18, 21, 22) translated the above inhibitory learning/retrieval model to exposure therapy to derive recommendations for therapists to optimize treatment effects. In this model, threat prediction error (rather than fear reduction) drives corrective learning so that an exposure will only be therapeutic to the extent that the patient’s fears don’t come true (a negative prediction error). The degree of negative prediction error is thought to determine the amount of corrective learning so therapists should conduct exposures in a way that achieves maximal negative prediction error (rather than fear reduction *per se*). Strategies to maximize negative prediction error included eliciting threat patient predictions and perceptions of the outcome, designing exposures to enable proper testing of threat predictions, encouraging patients to drop subtle avoidances during exposures, and sequencing exposures so they are more unpredictable. The inhibitory learning/retrieval model of exposure also implied that relapse (i.e., return of fear) may be prevented by exposure practice that is varied in context and well consolidated in memory.

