The goal of this study is to determine the sequelae of prediction error (both amount and type) during exposures on clinical outcomes in CBT for social anxiety disorder (SAD). This disorder is characterized by excessive fear and avoidance of social situations (57). CBT for SAD presents a good case for exploring exposure prediction error effects for several reasons. First, SAD is one of the most common anxiety disorders (58), meaning recruitment may be easier and any results will be pertinent to many therapists and patients. Second, CBT is widely used and efficacious for SAD (59). Third, evidence-based CBT treatments have exposure as a core treatment component in the form of a systematic approach toward feared social situations (60–64). Finally, at the time of study design, prediction error had not been studied explicitly in CBT for SAD. Our study has three aims:

(1) The primary aim of the current study is to explore whether threat prediction error experienced during exposures in and between sessions is related to session-by-session symptom changes. We will model the effects of threat prediction and outcomes separately rather than using difference scores while isolating within-person from between-person effects, with the former being of primary interest. We will sample both in-session and homework exposures in treatment by using smart-phone based ecological momentary assessment (EMA) and generate rich descriptive information about patient exposure experiences. We hypothesize that prediction errors will be common in treatment and that negative threat prediction error during exposures between sessions will predict symptom reduction between sessions. We hypothesize that positive prediction error during exposures between sessions will predict symptom increase between sessions.

(2) A secondary aim of the current study is to explore whether the average magnitude of prediction errors experienced during treatment is associated with treatment outcome. We hypothesize that patients who experienced a greater mean level of negative prediction error across all exposures in treatment will report fewer symptoms at the end of treatment and after 3 months.

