#### Threat outcome

Perception of threat outcome during a planned exposure is operationalized as the belief strength that predictions occurred during the exposure. Threat outcome (O) will be measured using parallel versions of the four O items which share the same scale (slider rating of strength belief from 0 = *“Not at all”* to 100 = “*Extremely*”) and content dimension (occurrence of threat), but different reference points (predicted vs. experienced). For example, the P item *“How strongly do you believe that your worst fears will happen during the activity?”* corresponds with the O item *“How strongly did you believe that your worst fears happened during the activity?”* Commensurate measurement of P and O enables meaningful interpretation of any joint effects they have on the outcome variables (47). The mean of belief strength ratings for the four O items will be used to assess the overall threat outcome for the specified exposure. The overall perceived actual aversiveness of a specified exposure will be assessed with a commensurate version of the expected aversiveness item in the pre-exposure section (i.e., *“How bad do you think the outcome of the activity was?”* on a scale of 0 = *“Not at all”* to 100 = *“Extremely”)*.

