## Discussion

This study will provide information about the frequency and type of prediction error experienced during exposure for SAD. It may help determine whether threat prediction error, as measured by self-report, predicts dynamic and long-term clinical outcomes in exposure for SAD. The study may also help to clarify the relationship between prediction error, surprise, and learning outcomes in the context of exposure. The above outcomes would contribute to evaluating the translation of extinction learning to exposure therapy.

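### If P and O are each standardized on their own mean and SD, the prediction-error count loses the average P-O gap, so the reported types come out near 50/50 and the 10% gate hardly discriminates

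*Protocol article*

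**What the plan says.** The Analysis section gives the construct first: "We operationalize prediction error as the discrepancy between threat prediction (P) and threat outcome (O) scores for an exposure". Before any model is fitted, the errors are to be counted and typed: "We will explore how many cases of prediction error and what type are present in the data before modeling". The counting rule is to "categorize a prediction error as an exposure where the standardized P and O scores differ by more than 0.5 standard deviation in either direction", and it is labelled descriptive. The next sentence makes the same count a condition for going on: "We will proceed with modeling prediction error effects if more than 10% of exposures meet the above prediction error criteria".

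Three other places bear on this rule:

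- **Introduction, on fear extinction.** Type is defined by direction against the person's own expectation: "negative threat prediction errors, defined as when the rate or severity of aversive outcomes is" lower than expected, with positive errors as the reverse.
- **Threat outcome.** P and O use parallel items on the same 0-100 slider, and the reason given is that "Commensurate measurement of P and O enables meaningful interpretation of any joint effects they have on the outcome variables".
- **Aim 1 and Discussion.** Aim 1 states "We hypothesize that prediction errors will be common in treatment", and the Discussion opens with the promise that "This study will provide information about the frequency and type of prediction error experienced during exposure for SAD".

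The article does not say whether standardization uses a separate mean and SD for P and for O or one common pair. It gives no mean, SD or correlation for either score.

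**The concern.** P and O were built on one metric so that P minus O can be read directly: above zero the exposure went better than predicted, below zero worse. Separate standardization sets both means to zero and discards that reading. An exposure is then judged against the sample's average gap, not against the participant's own prediction. If most exposures go better than feared, those that went better by less than the average amount are pushed towards the positive (worse than expected) category.

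Two outputs are at stake. One is the descriptive frequency and type of prediction error, which the Discussion lists first among the study's contributions. The other is the 10% gate, which is meant to establish that enough errors exist to model.

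**Working it through.** **Inputs.** The 0.5 SD cut and the 10% gate come from the Analysis section. Separate standardization, rough normality, and the values of r, the means and the SDs are assumptions, because the article gives none of them. The plan states no share of errors, so there is no planned figure to reproduce.

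**Step 1: share flagged under the rule.** With separate z-scores, zP - zO has mean 0 and variance 2(1 - r). The share flagged is 2 × [1 - Φ(0.5 / √(2(1 - r)))], half in each direction. The raw mean gap does not appear in the formula.

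| r | SD of zP - zO | 0.5 / SD | Share flagged | Each type |
|---|---|---|---|---|
| 0.3 | 1.183 | 0.423 | 67% | 34% |
| 0.5 | 1.000 | 0.500 | 62% | 31% |
| 0.7 | 0.775 | 0.645 | 52% | 26% |
| 0.9 | 0.447 | 1.118 | 26% | 13% |

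**Step 2: where the gate stops.** Setting the share to 10% gives 0.5 / SD = 1.645, so SD = 0.304 and r = 1 - 0.304² / 2 = 0.954. The gate passes for any r below that.

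**Step 3: the same data on the raw scale.** Assume mean P = 60, mean O = 35, both SDs 22, r = 0.5. Then D = P - O has mean 25 and SD 22 × √(2 × 0.5) = 22. Half an SD is 11 points.

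- Negative (better than predicted): P(D > 11) = Φ((25 - 11) / 22) = Φ(0.636) = 74%.
- Positive (worse than predicted): P(D < -11) = Φ(-36 / 22) = Φ(-1.636) = 5%.
- The planned rule reports 31% and 31%.

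**Step 4: who is mislabelled.** In this example zP - zO = (D - 25) / 22, so the rule calls an exposure positive when D < 25 - 11 = 14. Exposures with D between 0 and 14 went better than predicted but are labelled worse. Their share is Φ(-0.5) - Φ(-25 / 22) = 0.309 - 0.128 = 0.181. That is 18% of all exposures and 0.181 / 0.309 = 59% of those labelled positive. On the raw scale, 87% of exposures have O below P.

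**Step 5: does the bounded scale rescue it?** No. Simulating the Step 3 case with scores clipped to 0-100 still gives 31% and 31%, with about 58% of labelled positives having O below P. Skewed bounded scores also stayed near an even split (for example 36% against 31%).

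**Step 6: collinearity where the gate stops.** The two-predictor variance inflation factor is 1 / (1 - r²): about 11 at r = 0.954, about 17 at r = 0.97, and undefined at r = 1.

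**The case against.** **The text does not say the scores are standardized separately.** This is true. With one common mean and SD the gap is kept and the problem disappears. Separate z-scores are the ordinary reading, but it remains a reading, and the point is conditional on it.

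**The rule is descriptive and rests on cited methods.** The label does not remove the harm, because the description is itself a promised output and the same count gates the modelling. The citations cannot be checked here, and in any case they would not restore a gap removed from scores that share a metric.

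**The primary analysis does not use the classification.** This stands. Mean P and mean O enter as separate predictors, person-mean centred, and support requires two significant coefficients of opposite sign. A reader might infer that the primary coefficients are biased; nothing in the Analysis section supports that.

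**The gate is not shown to give wrong answers.** This largely stands. A reader might infer that the rule could halt the study when every exposure is a prediction error, for instance if each outcome fell exactly 25 points below prediction. There r = 1, P and O are perfectly collinear, and the planned two-coefficient model cannot be estimated, so stopping loses nothing. Step 6 shows the model is already strained at the break-even. (These are exposure-level correlations; the model uses person-centred interval means, whose correlation is unknown.) At r up to about 0.9 the planned and raw-scale rules both say proceed.

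**The rule does not formally decide whether errors are common.** This is also true: Aim 1 attaches no threshold to that word. The count is still the only evidence on frequency that the article describes.

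**Conclusion.** The point holds, conditional on separate standardization. Removal of the mean gap then follows for any data. The even split and the dependence on r alone also need roughly normal scores, though clipping and skew change the split little.

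The size depends on values the article does not give. The rule flags 26% to 67% of exposures for r from 0.9 down to 0.3. In the illustrated case it reports 31% and 31% where the raw scale gives 74% and 5%, and about 59% of the exposures it calls worse than expected went better than predicted. That contradicts the Introduction's definition of error type and makes the promised frequency and type misleading.

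The gate's weakness is that it hardly discriminates. It passes for any r below about 0.954 and cannot reveal that one type is scarce, although Aim 1 hypothesizes an effect of positive errors as well as negative ones. The harm is confined to the counts, the types and the gate.

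**What to change.** Replace the classification sentence with one on the common 0-100 metric: flag an exposure as a negative error when raw P - O exceeds +0.5 of one pooled SD, and as a positive error when it is below -0.5 of that SD, with the same mean and SD applied to both scores. A fixed number of points would serve equally well. State how the pooled SD is formed. In the example, averaging the two variances gives 22 and a cut of 11 points. Stacking P and O gives √(22² + 12.5²) = 25.3 and a cut of 12.7 points, which yields 71% and 4% in place of 74% and 5%.

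Report counts by type on that basis and apply the existing 10% rule to that count. Because a raw-scale gate can pass when P and O are nearly collinear, check their collinearity separately before fitting the model.

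If a common mean and SD was intended all along, one clause saying so settles the matter. Either way the cost is a sentence or two. The raw ratings are collected already, so no new data are needed and the primary model does not change.
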